###### a) Adolescent physical activity and sedentary behaviour

The Children's Leisure Activities Study Survey is used to assess physical activity and sedentary behaviours [44]. This has been developed for the Australian environment and is validated in 10–12 year olds.

###### b) Adolescent food intake and eating patterns

This questionnaire includes 15 food frequency questions on food and beverage items relevant to obesity [45] as well as questions on eating patterns and behaviours that were developed for an Australian study of adolescents' eating patterns and behaviours [46].

###### c) Adolescent psychosocial wellbeing

Several measures of adolescent psychosocial wellbeing are used including:

▪ The Harter Self-Perception Profile for Adolescents [47] which provides a measure of global self worth and perceived competence in eight specific domains, such as social acceptance, athletic competence and, physical appearance.

▪ Adolescents' perception of body image, including present and preferred body shape, is assessed using a simple visual scale that has been validated [48].

▪ The MacArthur Scale of Subjective Social Status, an adaptation of a 10-point vertical ladder scale, is used to evaluate social acceptance with adolescent peers [49].

▪ The Mental Health Inventory-5 (MHI-5), a 5 question mental health assessment component of the SF-36, is used to assess quality of life for adolescents [50].

###### d) Pubertal stage

Adolescents self-report their stage of pubertal maturation using the standard Tanner Stage line drawings for males or females [51] at baseline, and 12 and 24 months post-baseline.

###### e) Adolescent satisfaction with the program

At 2, 12, and 24 months post-baseline, all adolescents complete a questionnaire, adapted from one used by the investigators in another study involving obese pre-adolescent children [52], addressing the quality of service provided and whether participants would recommend the program to others. A separate questionnaire is used at 24 months post-baseline in the 'G+ATC' group which evaluates the types of ATC communication (i.e. telephone coaching, mobile phone SMS, e-mails) that adolescents found to be most useful.

##### iv) Parent/carer self completed questionnaires

At baseline parents/carers complete a short questionnaire regarding demographic characteristics. Parents/carers also complete a questionnaire to assess their satisfaction with the study interventions at 2, 12, and 24 months post-baseline, similar to the one completed by adolescents.

### Planned data analysis

Variables that are not normally distributed will be transformed to make them so, or non-parametric techniques will be used. Analysis of covariance will be used to test for differences in baseline characteristics by study arm and adjustment will be made to analyses as required. An estimation of intervention effect on outcome measures will be obtained at each follow-up observation (2, 12, & 24 months post-baseline) on an intention to treat basis. A mixed model will be used to test the average effect of the intervention after taking account of baseline covariates. A time-group interaction will be included to test whether the rate of change of BMI z-score is different between the 'G' and 'G+ATC' study arms. Planned contrasts will be used to measure between group differences at each evaluation time point. Randomisation should ensure distribution of ethnicity but ethnicity subgroup analysis and statistical adjustment will be made as required.

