#### Randomisation

A computer generated randomisation sequence, stratified for sex, age group (13–14 years; 15–16 years), and intervention site was provided by staff in the Clinical Epidemiology Unit, The Children's Hospital at Westmead. The trial manager is responsible for concealed allocation which involves preparing, for each intervention site, sex and age group, a set of consecutively numbered opaque envelopes containing the group allocation 'G' or 'G+ATC'. After participant consent is obtained the next numbered envelope is opened by a research assistant (at the abovementioned appointment to confirm eligibility), revealing the group allocation and this is recorded along with the individuals pre-assigned identification number. Outcome assessors are the only persons blinded to group assignment.

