#### Sample size

In adults, the clinical benefit of 5% relative weight loss is associated with improvements in HbA1c in Type 2 diabetes [33], blood pressure [34], total cholesterol and HDL cholesterol [35], and ovarian function in polycystic ovarian syndrome [36]. It could be reasonably assumed that adolescents will experience similar clinical benefits. Over a one year period, a clinically significant weight loss of 5% corresponds to a 0.4 unit change in BMI z-score, and a 5% reduction in waist circumference corresponds to a 0.2 unit reduction in waist circumference z-score. A sample size of 64 in each intervention arm will have 80% power to detect a 0.4 unit difference in mean change of BMI z-score from baseline to 2, 12 and 24 months follow-up in the two interventions (two group t-test, 0.05 two-tailed significance). Based on the results from our preliminary study, we have assumed the common SD is 0.8 for the change in BMI z-score, and that the calculated sample size is sufficient to detect a 0.2 unit change in waist circumference z-score, an 8% increase in HDL cholesterol, a 9% decrease in total cholesterol, a 7 mmHg and a 4 mmHg reduction in systolic and diastolic blood pressure, respectively, and a 15% increase in Harter global self-worth score [31]. To accommodate a 30% drop-out rate (based on adult studies), we aim to enrol 84 participants in each intervention arm.

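### Covariate adjustment is made to depend on tests of baseline differences between arms, which select on chance imbalance rather than prognostic value

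*Protocol article*

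**What the plan says.** All references are to the protocol article.

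- **Planned data analysis, selection rule:** "Analysis of covariance will be used to test for differences in baseline characteristics by study arm and adjustment will be made to analyses as required".
- **Planned data analysis, ethnicity:** the article notes that randomisation should balance ethnicity, then adds that "ethnicity subgroup analysis and statistical adjustment will be made as required".
- **Planned data analysis, model:** "A mixed model will be used to test the average effect of the intervention after taking account of baseline covariates". No covariate is named.
- **Randomisation:** the sequence is "stratified for sex, age group (13–14 years; 15–16 years), and intervention site", with concealed envelopes for each combination of these factors. Blocking is not mentioned.
- **Sample size:** "A sample size of 64 in each intervention arm will have 80% power to detect a 0.4 unit difference in mean change of BMI z-score", by a "two group t-test, 0.05 two-tailed significance". This calculation uses no covariates.

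**The concern.** In a randomised trial with concealed allocation, a baseline test asks whether chance produced a difference, and the answer is already known. What makes a covariate worth including is how strongly it predicts the outcome, and the test carries no information on that. A weak predictor that happens to differ is taken in. A strong predictor that happens to be balanced is left out.

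The rule fits poorly with the design. Stratification tends to balance sex, age group and site, so a trigger based on imbalance is unlikely to pick them. Yet an analysis that omits prognostic stratification factors gives up precision and, if the lists were blocked, reports standard errors that are too large. The baseline value of the outcome, often the most useful covariate, gets no privileged place either.

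At stake are precision and the credibility of a primary model whose terms are settled after looking at the data by arm.

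**Working it through.** **1. The plan's own figure.** Inputs from Sample size: difference 0.4, SD 0.8 ("we have assumed the common SD is 0.8 for the change in BMI z-score"), two-sided 0.05, 80% power. Standardised effect = 0.4/0.8 = 0.5. Normal approximation: n = 2 × (1.960 + 0.842)² / 0.5² = 62.8, so 63. The exact t-test gives 63.8, so 64 per arm, with 80.1% power. The stated 64 reproduces. It rests on an unadjusted test, so adjustment would add precision to it and does not alter it.

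**2. How often chance triggers adjustment.** The article states no threshold and no number of tests. Assuming p < 0.05 and k independent variables, P(at least one) = 1 − 0.95^k:

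| k | P(at least one) |
|---|---|
| 5 | 23% |
| 10 | 40% |
| 15 | 54% |
| 20 | 64% |

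Many of the listed measures are related (BMI and waist z-scores, the lipids, the self-perception domains), so these figures are illustrative only.

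**3. What adjustment could be worth.** If the covariates together correlate r with the outcome, residual variance falls by r², and the n per arm giving the same precision is about 64 × (1 − r²). All values of r are assumed.

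| r | Variance removed | Equivalent n per arm |
|---|---|---|
| 0.3 | 9% | 58.2 |
| 0.4 | 16% | 53.8 |
| 0.5 | 25% | 48.0 |

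**4. Does the rule find the useful covariates?** A simulation used 64 per arm, a standardised effect of 0 or 0.5, and 3,000 trials per scenario. It compared covariates selected at p < 0.05 with a fixed set (sex, age group, site, baseline covariate). Assumptions not in the article: 5 sites, six irrelevant covariates, a baseline covariate with r = 0.3, a single time point analysed by linear regression, and lists either in blocks of 4 or unblocked.

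| Lists | Variance explained by strata | Type I, selected | Type I, fixed | Power, selected | Power, fixed |
|---|---|---|---|---|---|
| Blocked | 5% | 0.044 | 0.048 | 81% | 85% |
| Blocked | 15% | 0.033 | 0.054 | 81% | 90% |
| Blocked | 30% | 0.020 | 0.042 | 84% | 95% |
| Unblocked | 5% | 0.050 | 0.052 | 79% | 83% |
| Unblocked | 15% | 0.048 | 0.058 | 79% | 87% |
| Unblocked | 30% | 0.038 | 0.050 | 80% | 94% |

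The Monte Carlo standard error of a 5% rate is √(0.05 × 0.95/3000) = 0.004.

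- **Selection of strata:** with blocked lists no stratification factor was selected in 24,000 trials. Without blocking, at least one was selected in about 14%.
- **Selection of the prognostic covariate:** it was picked in about 5% of trials, and no more often when its correlation was raised to 0.6.
- **Standard errors:** with blocked lists and strata explaining 30% of variance, the selected model reported a mean SE of 0.178 against a true 0.149. At 5% the gap was small (0.177 against 0.172).
- **Bias:** none seen. Mean estimates lay within 0.007 of the true value throughout.

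**The case against.** The strongest reply is that the article separately and unconditionally commits to a mixed model that takes account of baseline covariates. Those could include the stratification factors and the baseline outcome, and naming them is detail a condensed article leaves to a fuller document. Part of this stands. The absence of a list is not the finding, and a reader should not infer that the plan will omit sex, age group and site, because it does not say so. But the only selection rule the article states is the baseline test, and an unnamed set of covariates does not displace it. A later document would have to reverse that rule rather than fill it in.

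Other points also stand:

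- A reader might infer that the strata could never be selected. Blocking is not stated, and without it they sometimes would be.
- The outcomes are age- and sex-specific z-scores (Anthropometry and blood pressure), so sex and age group are partly standardised out already.
- Baseline enters in part through the change measure used in Sample size. A change score fixes its coefficient rather than estimating it, so some precision may remain to be gained.
- The wording sets no threshold, so selection by significance is the natural reading rather than the only one. An undefined trigger, however, leaves more discretion, not less.

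**Conclusion.** The point holds as one of efficiency and pre-specification. The stated rule selects covariates on chance imbalance and is unlikely to select the stratification factors, particularly if lists are blocked. The result is a data-dependent model, standard errors that may be too large, and lost precision.

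A reader might go further and infer bias or an inflated type I error. The check does not support that for a fixed selection rule: estimates were unbiased, and type I error under selection was 0.020 to 0.050.

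The size is uncertain. The 9% to 25% reduction in residual variance follows from an assumed r of 0.3 to 0.5. The simulated power differences rest on assumed sites, blocking and explained variance, and on a single time point rather than the planned repeated-measures model. The lower end is the more plausible for whatever sex and age group contribute. The change is worth making because it is nearly free, not because the primary result would otherwise be invalid.

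**What to change.** Drop the baseline tests as a way of choosing covariates; baseline characteristics can be described by arm without them. Pre-specify, before the outcome data are analysed, a mixed model with arm, visit, arm-by-visit, the baseline value of the outcome, sex, age group in its two randomisation levels, and intervention site. The timing is tied to the analysis because the article blinds only the outcome assessors. The number of sites is not given, so state in advance that small sites will be pooled, or that site will be a random effect if there are many. Pre-state any ethnicity analysis as exploratory, with no data-driven adjustment of the primary model.

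The cost is the rewording of a few sentences in Planned data analysis. The stratification factors and baseline outcome values are already recorded, and the sample size does not change.

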## Aims and hypotheses

The primary aim of the study is to determine the effect of ATC to usual treatment on body mass index (BMI) z-score and waist circumference z-score in overweight and obese adolescents aged 13–16 years (at baseline) who participate in a community-based weight management program (the Loozit^® ^group program). Adolescents enrolled in the study are randomised to receive one of the following two interventions: the Loozit^® ^group program (G); or the Loozit^® ^group program + additional therapeutic contact (G + ATC). ATC includes a combination of telephone coaching, and mobile phone SMS and/or e-mail messages. It is hypothesised that:

1. compared to baseline, both the G and the G+ATC interventions will result in a clinically relevant and a statistically significant:

a) reduction in BMI z-score and in waist circumference z-score (primary outcomes) at 2, 12 and 24 months post-baseline;

b) improvement in other important outcome measures in weight management including metabolic profile indicators, eating patterns, physical activity, sedentary behaviour, and psychosocial well-being (secondary outcomes) at 2, 12 and 24 months post-baseline; but that

2. the G+ATC intervention, relative to the G intervention, will produce a clinically relevant and a statistically significant greater reduction in the primary and secondary outcomes outlined above at 12 and 24 months post-baseline, as well as better retention in the program.

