#### 2) Additional therapeutic contact for adolescents (ATC)

##### i) Background

In addition to the Loozit^® ^group program 'G', participants in the 'G+ATC' study arm also receive a modest level of additional therapeutic contact (ATC) in phase 2 only. ATC is planned communication from the group facilitator to the adolescent via telephone coaching plus a mode of electronic communication i.e. mobile phone SMS or e-mail messages, or both, according to adolescent preference. The aim of ATC is to enhance adolescents' knowledge, skills and confidence to initiate and maintain required changes in dietary and activity behaviours. Because mobile phone SMS and e-mail interventions are relatively new technologies, there is little evidence in the child and adolescent weight management literature on the optimum frequency of contact and level of interaction in using these technologies, especially in the context of a program that already offers extended therapeutic contact in the form of group sessions and telephone coaching. A primary consideration in the design of the ATC schedule was that it was in keeping with the sustainability aspects of the Loozit^® ^group program. Parents/carers of adolescents in the 'G+ATC' study arm do not receive any form of ATC.

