### Measures

#### Schedule

The primary outcomes are adolescent BMI z-score and waist circumference z-score. The secondary outcomes are metabolic profile indicators, physical activity, sedentary behaviour, food intake, eating patterns, and various aspects of adolescent psychosocial wellbeing. All these outcomes are measured at baseline, 2 months post-baseline (end of phase 1), 12 months post-baseline (almost half-way through phase 2), and 24 months post-baseline (at the end of phase 2). In addition, at 2, 12 and 24 months post-baseline, adolescent and parent/carer satisfaction with the program is measured by questionnaire.

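### The 2-month visit precedes all additional therapeutic contact, yet it is in the between-arm power claim and, on the natural reading, in the average-effect test

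*Protocol article*

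**What the plan says.** **Timing of ATC.** Participants in the G+ATC arm "also receive a modest level of additional therapeutic contact (ATC) in phase 2 only" (Additional therapeutic contact for adolescents, Background). The Measures section (Schedule) places the first follow-up at "2 months post-baseline (end of phase 1"). According to Adolescent ATC preferences, the preferences and contact details needed to deliver ATC are first collected at that visit. Until then both arms are offered the same group programme.

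**Between-arm hypothesis.** Hypothesis 2 in Aims and hypotheses expects from G+ATC a "greater reduction in the primary and secondary outcomes outlined above at 12 and 24 months post-baseline". It does not name 2 months. Hypothesis 1, on change from baseline within each arm, does.

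**Power.** Sample size states: "A sample size of 64 in each intervention arm will have 80% power to detect a 0.4 unit difference". The outcome is the change in BMI z-score, tested between the arms by a two-sample t-test at a two-sided 5% level. The claim is made for the change "from baseline to 2, 12 and 24 months follow-up in the two interventions".

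**Analysis.** Planned data analysis estimates the intervention effect "at each follow-up observation (2, 12, & 24 months post-baseline"). The next sentence is "A mixed model will be used to test the average effect of the intervention after taking account of baseline covariates". A time-by-group interaction and a between-arm contrast at every visit follow. The section does not say which visits enter the average, how they are weighted, or which of these tests is decisive.

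**The concern.** The trial asks whether ATC adds anything to the group programme. A comparison of arms at 2 months cannot answer that, because no ATC has been delivered. Hypothesis 2 respects this; the power sentence and the analysis section do not.

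Two things are at stake. First, the power sentence treats 2 months as a time point at which the trial could detect an ATC effect, and none can exist there. Second, if the average effect covers all three follow-ups, a real effect at 12 and 24 months is mixed with a visit carrying no ATC effect. The estimate then shrinks and the test loses power. Because no test is named as primary, and the average is the first model-based test listed, one cannot assume that an undiluted contrast will decide the trial.

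**Working it through.** **Inputs from the protocol article (Sample size):** difference 0.4, SD of change 0.8, two-sided alpha 0.05, two-sample t-test, 64 evaluable per arm.

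**Assumptions that are not in the document:** true ATC effects of 0 at 2 months and 0.4 at 12 and 24 months; SD 0.8 at every visit; equal visit weights; a common correlation r between change scores at different visits.

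**Step 1: the plan's own figure.** The standardised difference is 0.4 / 0.8 = 0.5. The t-test needs 63.8 per arm, so 64, and power at 64 is 80.1%. The stated figure reproduces for a contrast at a single visit.

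**Step 2: the pooled effect.** (0 + 0.4 + 0.4) / 3 = 0.267, against 0.4 for the mean of 12 and 24 months.

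**Step 3: SD of the averages.** For three visits it is 0.8 × √((1 + 2r)/3); for two visits it is 0.8 × √((1 + r)/2).

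**Step 4: power at 64 per arm (noncentral t).**

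| r | SD, three visits | Effect/SD | Power, 2+12+24 months | Power, 12+24 months |
|---|---|---|---|---|
| 0.3 | 0.584 | 0.456 | 72.7% | 93.6% |
| 0.5 | 0.653 | 0.408 | 63.0% | 90.0% |
| 0.7 | 0.716 | 0.373 | 55.3% | 86.1% |

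Against the stated 80%, the three-visit average falls short by about 7, 17 and 25 points.

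**Step 5: where the shortfall begins.** The three-visit average matches the planned power when its effect/SD is 0.5, so when its SD is 0.267 / 0.5 = 0.533. Then (1 + 2r)/3 = (0.533/0.8)² = 4/9, which gives r = 1/6. Below that correlation there is no shortfall against 80%; at r = 0 power is 90%. So low a value is unlikely, because change scores share the same baseline. If the raw scores have equal variance σ² and a common correlation c, two change scores have covariance σ²(1 − c) and variance 2σ²(1 − c), so r = 0.5 whatever c is.

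**Step 6: sensitivity to the weights.** One third is the dilution under equal weights only.
- Weighting by observed visits, with assumed attendance of 95%, 80% and 70%, gives 2 months a weight of 0.95 / 2.45 = 0.39, so a dilution of about 39%.
- A model with a single treatment term and precision weights, with an assumed SD of change of 0.6 at 2 months and 0.8 later, gives 2 months 56% to 90% of the weight for r from 0.3 to 0.7.

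**The case against.** The strongest reply is that undiluted tests are already planned. The contrasts at 12 and 24 months match hypothesis 2, and the sample size was set for exactly such a contrast. This stands: those contrasts and the 64 per arm are untouched.

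It is also fair that the analysis section never says outright that 2 months enters the average. Inclusion is inferred from the preceding sentence, which lists all three visits, and from the lack of any exclusion. An unseen analysis plan may define the contrast differently. That reply does not cover the power sentence, which names 2 months explicitly and is a two-group comparison, so it cannot be read as serving the within-arm hypothesis.

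Four stronger readings are tempting and should not be drawn:
- **That the effect is diluted by a fixed third.** The weights are not stated, and other weightings give other figures.
- **That power drops by 27 to 31 points.** That compares the three-visit average with a two-visit average at 90% to 86% power (r = 0.5 to 0.7), which the protocol never claimed. The fair benchmark is its own 80%.
- **That a 2-month difference would be reported as an ATC effect.** The article calls both arms interventions, hypothesis 2 leaves 2 months out, and no sentence attributes a 2-month difference to ATC.
- **That the arms must be identical at 2 months.** Only the ATC effect is zero. Allocation is revealed before phase 1 and only outcome assessors are blinded (Randomisation). The arms meet on separate weeknights (Table 1, footnote b) and are never combined (Practical considerations). Differences from group, evening or knowledge of allocation are therefore possible.

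**Conclusion.** The concern holds in limited form. Including 2 months in the between-arm power claim contradicts both hypothesis 2 and the ATC schedule; this follows from the text alone. Pooling 2 months in the average effect is the natural but inferred reading. If it is followed, a true 0.4 effect at both later visits is estimated as 0.267, with about 73% to 55% power for r from 0.3 to 0.7, under the assumed equal weights and constant SD. The problem is confined to the average-effect test and the 2-month claims. It does not call into question the sample size formula for a single visit, the data collection, or the 12- and 24-month contrasts.

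**What to change.** 1. **Sample size:** remove 2 months from the between-arm power sentence, leaving 12 and 24 months. The figure of 64 per arm does not change.
2. **Planned data analysis:** fit visit as a categorical factor, and define the average ATC effect as the arm contrast over 12 and 24 months only, with the weights stated, in line with hypothesis 2. Under the assumptions above with equal weights, this average has 94% to 86% power for r from 0.3 to 0.7, and 80% even at r = 1.
3. **2 months:** keep the visit for the within-arm description of phase 1 that hypothesis 1 needs, and report the 2-month arm contrast only as a pre-ATC check.
4. **Do not constrain the arms to be equal at 2 months.** If a phase 1 group effect exists, that constraint could bias the later contrasts.

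The cost is a few sentences, with no additional participants, visits or data. The change should be made before outcomes are compared by arm.
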